#### Health and social functioning

Trained survey interviewers will update information from study Phase 1 on education, occupational status, health history and self-assessment of health status, quality of life measures, current mental health, substance use, family, peer and partner relationships and other aspects of social functioning. Interviews (2 to 3 h) will be conducted in private.

#### Parent/significant other report

To gain a further perspective on the young person’s health and functioning, a telephone interview will be conducted with a parent or significant other person nominated by the respondent. These interviews will gather a third person perspective on aspects of the young person’s health and health history, education and transition to adult roles, the young person’s behaviour and personality, social and partner relationships and related issues. Interviews will take 35–45 min and will be conducted by trained survey interviewers who are independent of the survey team interviewing the young person, but are not blinded their background.

#### Magnetic resonance imaging

We will undertake a cranial MRI scan on all participants who were born at <28 weeks gestation and a random sample of the VLBW cohort to bring the total having MRI scans to 150, plus a random 50 controls. Images will be acquired using a 3-Tesla GE scanner on the Christchurch campus and analyses undertaken by experienced staff blinded to the participants’ background. Scanning will take a total of 35–45 min comprising:▪ Clinical data – T2 and T2 FLAIR images as part of standard clinical protocol for purposes of a radiologist read/referral/exclusion and qualitative scoring▪ T1-weighted images will be used to assess brain growth and tissue distribution▪ Diffusion Tensor imaging (DTI) will assess white matter microstructural development (fractional anisotropy).▪ Arterial Spin Labelling (ASL) – a non-invasive functional measure of cerebral blood flow that produces quantification of cerebral perfusion and has good concordance with ^15^O-PET [56]▪ Resting State Functional Connectivity (fcMRI) which provides a method to evaluate regional interactions in the brain.Both ASL and fcMRI may be clinically useful as biomarkers for individuals at increased risk of later cognitive impairment. This protocol, with the addition of ASL, is the same as that being used at 12 years of age in a cohort of former <32 week gestation children, who also had MRI scans at term equivalent, [12] and this may allow early clues as to longitudinal trajectories of brain injury and neural plasticity.

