## Design and methods

### Study population

The case sample will comprise a minimum of 250 members of the 1986 NZ National VLBW cohort (77 % of survivors). In Phase 1 the proportion (%) of the 230 survivors seen and other survivors not assessed (94) who were <1000 g was 25.2 and 27.1; were <28 weeks is 24.8 and 24.0; are male is 47.0 and 52.1; are Maori is 26.1 and 22.1; had moderate/severe disability at 7 to 8 years is 10.3 and 6.7 – all being not significantly different. Outcomes for the VLBW cohort will be assessed against a comparison sample of 100 same age term controls recruited via a process of peer nomination and random sampling from electoral rolls, ensuring balance with respect to the gender, ethnicity and regional distribution of the sample.

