### Statistical analysis and statistical power

The collected data will enable two types of analyses to be conducted. Between group comparisons: The principal analyses will examine between group differences in outcome (health, neurocognitive assessments, social functioning), using standard statistical analyses: chi square for differences in proportions; *t*-test for independent samples or analysis of variance for differences in means of continuous outcomes; Poisson or negative binomial regression for differences in rates. Where outcome data are non-normally distributed appropriate data transformations (eg logarithmic) may be conducted. The VLBW group may be further subdivided to test for differential effects by severity of disability at age 7 to 8, or by birthweight or gestation. Comparisons may be further adjusted if necessary for between group differences in family background characteristics using regression methods based on the generalised linear model [58]. Assuming a minimum of 250 recruits from the VLBW cohort and 100 controls, the study will have 80 % power at alpha = .05 to detect differences between groups of 30 SD or greater on continuous outcomes, and ORs in the region of 2.0–3.5 for dichotomous outcomes (depending on the base rate) [59]. This suggests the study will have adequate power to detect effect sizes in the small to moderate range. These differences are well within the anticipated effect sizes based on existing reports [17, 18]. Subdividing the VLBW group (for example by level of prior disability) is unlikely to compromise study power since the effect sizes are likely to increase for more extreme groups.

Outcome trajectories amongst the VLBW cohort: For a number of outcomes, for example visual, physical growth, it will be possible to examine across time continuities and/or trajectories in outcome from childhood to adulthood within the VLBW cohort. Depending on the outcome under consideration, analysis methods may range from simple tabular methods documenting outcome in young adulthood conditional on childhood status, to simple regression models predicting outcome in adulthood from measures in childhood, to more complex methods for repeated measures data based on a generalised estimating equation approach [60] to model changes in outcome trajectory.

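### The MRI subset over-represents births before 28 weeks (about 41% of scanned cases against 25% of the cohort), so the equal-weight comparisons named would not give cohort-level MRI estimates

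*Protocol article*

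**What the plan says.** The MRI section of the protocol article defines the cases to be scanned as "participants who were born at <28 weeks gestation and a random sample of the VLBW cohort to bring the total having MRI scans". Everyone in the first of these groups is included, the target is 150 cases, and 50 controls are drawn at random. The abstract describes the same scheme.

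The last hypothesis under the first aim expects more structural brain abnormality in adults born VLBW than in full-term peers. It is stated for the VLBW group as a whole, not for those born before 28 weeks.

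The statistical section describes its principal analyses as standard between-group comparisons: "chi square for differences in proportions", a t-test or analysis of variance for means, and Poisson or negative binomial regression for rates. Two options follow. The VLBW group "may be further subdivided to test for differential effects" by earlier disability, birthweight or gestation, and comparisons may be "adjusted if necessary for between group differences in family background characteristics". Neither weighting nor standardisation for the MRI sampling is mentioned.

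**The concern.** Taking everyone in one gestation group and a fraction of the rest is a legitimate design and gives more information on the most immature survivors. But the 150 scanned cases are then not a simple random sample of the VLBW participants. If they are pooled and compared with controls by the tests listed, the result describes a group with an artificially high share of births before 28 weeks.

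At stake are the figures a reader would take from the MRI work: the prevalence of abnormality among VLBW adults and the size of their mean difference from term-born peers. The distortion is systematic. Recruiting more cases does not shrink it: with the MRI total fixed at 150, higher enrolment raises the over-representation.

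**Working it through.** The article gives no power or precision figure for the MRI subset, so there is none to reproduce. Its sampling inputs can be checked and carried through.

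**Inputs**
- Cases: "The case sample will comprise a minimum of 250 members of the 1986 NZ National VLBW cohort", given as 77% of survivors. Check: 250/324 = 77.2%.
- Births before 28 weeks, as percentages of the 230 survivors seen and the 94 not seen in Phase 1 (Study population): "were <28 weeks is 24.8 and 24.0". Combined: (0.248 × 230 + 0.240 × 94)/324 = 79.6/324 = 24.6%, so 24.8% is a fair figure for participants and for all survivors.
- MRI totals: "to bring the total having MRI scans to 150, plus a random 50 controls".

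**Sampling fractions at N = 250**
- Born before 28 weeks: 0.248 × 250 = 62, all scanned.
- Others: 250 − 62 = 188, of whom 150 − 62 = 88 are scanned; 88/188 = 46.8%.
- Share born before 28 weeks: 62/150 = 41.3% of scanned cases against 24.8% of participants, an excess of 16.5 points.

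**Other recruitment totals, same 24.8%**

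| Cases | <28 weeks | Others scanned | Share of MRI cases born <28 weeks |
|---|---|---|---|
| 230 | 57 | 93/173 = 53.8% | 38.0% |
| 250 | 62 | 88/188 = 46.8% | 41.3% |
| 276 | 68 | 82/208 = 39.4% | 45.3% |

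**Effect on a pooled mean difference.** Let d1 and d2 be the differences from controls, in SD, for births before 28 weeks and for the others. The cohort value is 0.248·d1 + 0.752·d2, and the equal-weight value is 0.413·d1 + 0.587·d2. Their gap is 0.165·(d1 − d2). The documents give no MRI effect by gestation, so d1 and d2 are assumptions.

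| d1 / d2 (assumed) | Cohort value | Equal-weight value | Gap |
|---|---|---|---|
| 0.4 / 0.4 | 0.400 | 0.400 | 0 |
| 0.6 / 0.4 | 0.450 | 0.483 | +0.033 (+7%) |
| 0.8 / 0.4 | 0.499 | 0.565 | +0.066 (+13%) |
| 1.0 / 0.4 | 0.549 | 0.648 | +0.099 (+18%) |
| 0.3 / 0.5 | 0.450 | 0.417 | −0.033 (−7%) |

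**Effect on a prevalence, same method.** With assumed rates of 40% and 20%, the pooled figure is 28.3% against a cohort value of 25.0%. With 60% and 20% it is 36.5% against 29.9%.

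**Against sampling error.** The standard error of a difference for 150 against 50 is √(1/150 + 1/50) = 0.163 SD. Gaps of 0.033, 0.066 and 0.099 SD are about 0.2, 0.4 and 0.6 standard errors.

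**Cost of weighting at N = 250.** Weights are 1 and 188/88 = 2.14.
- Effective VLBW n = (Σw)²/Σw² = 250²/(62 + 88 × 2.14²) ≈ 135.
- Standard-error ratio = √(1/134.8 + 1/50)/√(1/150 + 1/50) = 1.014.
- Difference detectable with 80% power at two-sided 5%: 0.457 SD unweighted, 0.464 SD weighted.
- At N = 276 the effective n is about 128 and the standard error rises by about 2%.

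**The case against.** The strongest reply is that the error is read from silence. The list of tests is generic, MRI is not named in it, the article condenses a fuller protocol, and sampling weights are ordinary content for an analysis plan that is not shown. A reader might infer that the sponsor has chosen an unweighted MRI analysis. The article does not say so, and a fuller plan could contain weights. What remains is that the article itself fixes the unequal sampling, states the hypothesis for the whole VLBW group, and names principal comparisons that do not match that sample.

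A second reply is that subdivision by gestation is already foreseen. It is, and it would supply the separate results by gestation group. But it is optional, and it leaves the pooled estimate as it was. The optional adjustment covers family background only. Gestation as an ordinary covariate would not repair the contrast either, because every control is term-born and the groups do not overlap on it.

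Third, a reader might infer that MRI differences are bound to be inflated. The documents do not establish that. The statistical section argues that subdivision will not harm power "since the effect sizes are likely to increase for more extreme groups", but this is a general remark illustrated by prior disability. The Background reports behavioural and school differences that widened at lower birthweight, which is not MRI evidence, and gives white-matter findings for very preterm infants as one group. A gradient is the article's general premise; for MRI it remains an assumption.

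Fourth, the hypothesis test is not undermined. If neither gestation group differs from controls, oversampling one of them does not create false positives. This stands.

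A reader might also extend the point to associations between MRI measures and other outcomes. That does not follow. Selection is on a known baseline variable, so associations conditional on gestation are not biased by it, and marginal ones shift only if gestation confounds or modifies them.

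**Conclusion.** The point holds for cohort-level MRI estimates. As written, the plan yields a pooled VLBW group with about 41% born before 28 weeks (38 to 45% for 230 to 276 cases) against 25% in the cohort, so pooled prevalences and mean differences would not describe the population named in the hypothesis.

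That mismatch rests on the article's own figures and on complete scanning of those born before 28 weeks. The direction and size of the resulting bias rest on an assumed gradient. It is upward by about 7 to 18% of the effect if the <28-week effect is 0.6 to 1.0 SD against 0.4 SD in the others, zero if effects are equal, and downward if the gradient runs the other way. In every case shown it is below one standard error.

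Severity is moderate. It concerns one hypothesis of twelve, leaves the null test intact, and can be corrected at analysis because gestation was recorded at birth.

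**What to change.** State that whole-cohort MRI prevalences, means and differences from controls use inverse-sampling-probability weights for the VLBW cases, with robust standard errors. The weights should come from the realised scanned fractions in each gestation group: 1 for births before 28 weeks if all are scanned, and about 2.1 for the others at N = 250. Controls, being a simple random subset, keep a constant weight. Standardising the two group-specific results to the cohort's gestation mix is an acceptable alternative. Report results for <28 and ≥28 weeks separately alongside the pooled figure, and settle the weighting before MRI results are seen.

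The abstract says scans will be offered, so some may be declined. Realised fractions then absorb different uptake between the gestation groups, on the assumption that uptake is unrelated to outcome within each group.

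The cost is one sentence and one weight variable, an effective VLBW sample of about 135 instead of 150, and standard errors about 1 to 2% larger. No change to recruitment or to the scanning scheme is needed.

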### Additional studies

Although not part of the primary protocol for the New Zealand 1986 VLBW Follow-up Study, we will also undertake two additional studies with separate funding.DNA methylation and outcomes in VLBW young adults. We will investigate whether young adults born with VLBW have differences in DNA methylation at specific sites in the genome (in peripheral blood samples), compared with a matched normal birthweight group, and whether these traits are associated with growth and metabolic health outcomes as young adults. Separate consent is required for this study, which also requires an additional 10 ml blood sample be taken.C type Natriuretic Peptide (CNP) and vascular risk in VLBW young adults. CNP is a paracrine vasoprotective peptide secreted by the vascular endothelium, and which has anti-inflammatory actions in rodents and has been shown to be atheroprotective. Very little CNP normally enters the circulation but a stable product of the prohormone (amino terminal proCNP, NTproCNP) can be readily measured in plasma and serves as a marker of CNP production in tissues. Recent studies by the Christchurch group have defined the normal age and gender related ranges of plasma NTproCNP concentration in 250 healthy adult subjects without known history of cardiovascular disorder [57]. We will compare the plasma NTproCNP concentrations in VLBW young adults and term born controls and investigate their relationship with individual vascular risk factors and with adult height.

### Statistical analysis and statistical power

The collected data will enable two types of analyses to be conducted. Between group comparisons: The principal analyses will examine between group differences in outcome (health, neurocognitive assessments, social functioning), using standard statistical analyses: chi square for differences in proportions; *t*-test for independent samples or analysis of variance for differences in means of continuous outcomes; Poisson or negative binomial regression for differences in rates. Where outcome data are non-normally distributed appropriate data transformations (eg logarithmic) may be conducted. The VLBW group may be further subdivided to test for differential effects by severity of disability at age 7 to 8, or by birthweight or gestation. Comparisons may be further adjusted if necessary for between group differences in family background characteristics using regression methods based on the generalised linear model [58]. Assuming a minimum of 250 recruits from the VLBW cohort and 100 controls, the study will have 80 % power at alpha = .05 to detect differences between groups of 30 SD or greater on continuous outcomes, and ORs in the region of 2.0–3.5 for dichotomous outcomes (depending on the base rate) [59]. This suggests the study will have adequate power to detect effect sizes in the small to moderate range. These differences are well within the anticipated effect sizes based on existing reports [17, 18]. Subdividing the VLBW group (for example by level of prior disability) is unlikely to compromise study power since the effect sizes are likely to increase for more extreme groups.

Outcome trajectories amongst the VLBW cohort: For a number of outcomes, for example visual, physical growth, it will be possible to examine across time continuities and/or trajectories in outcome from childhood to adulthood within the VLBW cohort. Depending on the outcome under consideration, analysis methods may range from simple tabular methods documenting outcome in young adulthood conditional on childhood status, to simple regression models predicting outcome in adulthood from measures in childhood, to more complex methods for repeated measures data based on a generalised estimating equation approach [60] to model changes in outcome trajectory.

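### Principal group comparisons are unadjusted although controls are balanced on sex, ethnicity and region; adjusting for these factors is a cheap gain, and family background belongs in a pre-specified second model

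*Protocol article*

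**What the plan says.** Under Statistical analysis and statistical power, the protocol article lists the principal between-group analyses as "chi square for differences in proportions; *t*-test for independent samples or analysis of variance for differences in means of continuous outcomes". Rates are to be compared by Poisson or negative binomial regression, with no covariates named. Adjustment is a later, optional step through the generalised linear model: "Comparisons may be further adjusted if necessary for between group differences in family background characteristics". No criterion for when it becomes necessary is given, and sex, ethnicity and region are not in that sentence.

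Under Study population, controls come from peer nomination and electoral-roll sampling, "ensuring balance with respect to the gender, ethnicity and regional distribution of the sample". The Background section describes the same recruitment for the Phase 1 controls. This is balance at group level, not individual matching.

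The power statement rests on 250 VLBW adults and 100 controls, with an alpha of 0.05, and names no covariates. Its target for means, at 80% power, is worded "to detect differences between groups of 30 SD or greater on continuous outcomes".

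**The concern.** Two separate things are at stake.

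**Precision.** Factors balanced by design are nearly unrelated to group membership. Where they also predict a continuous outcome, adjusting for them shrinks the standard error of the group difference at almost no cost. Height, lung volumes and left ventricular mass are all measured under Procedures, and all depend on sex. A t-test on such an outcome carries the between-sex variance in its error term, although sex is known for everyone.

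**Confounding.** VLBW birth is not randomised, and recruitment is not said to balance family background. The hypotheses cover education, welfare dependence, social functioning and cognition, where social background can influence both the exposure and the outcome. The Background section itself gives weight to IQ differences that persist after confounders are controlled. With adjustment optional and its trigger undefined, a reader of the results cannot know in advance which contrasts will be adjusted, or for what.

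**Working it through.** **Inputs from the article:** 250 VLBW adults, 100 controls, 80% power, alpha 0.05 (sidedness not stated; taken as two-sided). The detectable difference is printed as 30 SD and is read here as 0.30 SD, assuming a lost decimal point. **Inputs assumed, because the article gives none:** R², the share of outcome variance within groups explained by the covariates; Rg², the share of group membership they explain; and, for confounding, the imbalance and the covariate–outcome correlation.

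**1. The plan's own figure.** In SD units, SE = √(1/250 + 1/100) = √0.014 = 0.1183.
- Two-sided power at 0.30 SD: Φ(0.30/0.1183 − 1.960) = 71.8% (71.5% by the exact t).
- Detectable difference at 80% power: (1.960 + 0.842) × 0.1183 = 0.331 SD (0.332 exact), so about 0.33 SD.
- One-sided alpha of 0.05 would give 81.3%, and an equal 175/175 split would give 80.1%, but the article states neither.
- The odds-ratio range does reproduce two-sided: 2.00 at a 30% control rate and 3.43 at 5%.

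The mismatch at 0.30 SD is a separate matter. Here 0.33 SD serves only as the unadjusted baseline.

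**2. Adjusting for the balanced factors (continuous outcomes).** The adjusted SE is 0.1183 × √((1 − R²)/(1 − Rg²)). For balanced factors Rg² is about 0.

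| Assumed R² | Detectable difference, SD | Power at 0.30 SD |
|---|---|---|
| 0 | 0.331 | 71.8% |
| 0.05 | 0.323 | 73.9% |
| 0.10 | 0.314 | 76.2% |
| 0.20 | 0.296 | 80.9% |
| 0.30 | 0.277 | 85.8% |

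The R² needed for 80% power at 0.30 SD is 1 − (0.30/0.3315)² = 0.18.

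**3. Covariates that differ between groups.** Family background may be related to group, and the gain then shrinks. With Rg² = 0.05, R² = 0.10 gives 0.323 SD and 74.1% power. R² = 0.05 gives 0.331 SD and 71.8%, which is no gain. The case for family background therefore rests on confounding, not precision.

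**4. Size of possible confounding in an unadjusted mean difference.** Bias = imbalance in SD × correlation with outcome. The low end is 0.2 × 0.3 = 0.06 SD and the high end is 0.3 × 0.4 = 0.12 SD, or 20% to 40% of 0.30 SD. If the difference net of the confounder were zero, the nominal 5% test would reject 8.0% to 17.4% of the time. These values are illustrative.

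**5. Binary outcomes.** The square-root formula does not carry over. Covariates do not shrink the standard error of a logistic log odds ratio, so any gain lies in test power or in standardised estimates.

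**The case against.** The article is a condensed summary that already provides for regression adjustment, and the covariate list for each outcome can properly sit in an analysis plan that is not shown. That stands for the list. It does not cover the ranking, which the article does state: unadjusted comparisons are principal and adjustment is optional.

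The unadjusted contrast is also a legitimate descriptive quantity. The first aim is to assess how the VLBW cohort fares against term-born peers, and a health service may want exactly that. Leaving out balanced factors does not invalidate the test; if anything it is conservative. This stands, and it is why the unadjusted result should remain on show.

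The precision gain rests on assumed R² values. Nothing in the article shows that sex, ethnicity and region explain much of the variance in education, mental health, social functioning or cognition. This also stands: the gain should be expected mainly in strongly sex-dependent physical measures.

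Two stronger readings are tempting and are not supported:
- A reader might infer that the headline result will turn on a significance test for imbalance. The article describes no such test. Even under that reading, simulation with one covariate (imbalance 0.2 to 0.3 SD, correlation 0.3 to 0.4) gave a type I error of 5.3% to 5.6%, against 5.0% when always adjusting.
- A reader might infer that every covariate needed is already held. Sex, ethnicity and region must be known to achieve the balance. Childhood socio-economic data are not documented for controls. Only 69 controls were recruited in Phase 1, so at least 100 − 69 = 31 of the planned 100 would be new.

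**Conclusion.** The point holds as a worthwhile, low-cost improvement to a stated analysis choice. It does not show that the planned tests are invalid.

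For continuous outcomes, including the balanced factors would lower the detectable difference from about 0.33 SD to about 0.31 SD at an R² of 10% and about 0.30 SD at 20%, with little change at 5% or less. These figures assume two-sided testing, 250 and 100 participants, and covariates unrelated to group. They do not apply to the log odds ratio for binary outcomes.

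For family background the reason is confounding in a non-randomised comparison, chiefly for education, welfare and cognition. Its size cannot be derived from the article; the 0.06 to 0.12 SD range only shows what moderate assumptions would imply. What needs correcting is a discretionary adjustment with no stated trigger.

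**What to change.** 1. Make the principal estimate the group coefficient from the generalised linear model already cited, adjusted for sex, ethnicity and region for every outcome where event counts allow. Report the unadjusted comparison beside it.
2. Replace the optional adjustment sentence with a pre-specified second model that adds named family-background variables available in both groups, reported whatever the observed imbalance.
3. Before naming those variables, check which are recorded for controls as well as for the VLBW cohort, and how completely. The Phase 1 interview on social background and the parent or significant-other interview are the obvious places to look.

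The first change costs wording and routine regression on factors already used in recruitment. The second may require collecting some family-background data retrospectively from controls, and missing values there would fall on the smaller group. Rare binary outcomes will support fewer covariates, so the reduced set for those should be stated in advance.

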We hypothesise that within the VLBW cohort:8.Young adults who were characterised by significant disability/cognitive impairment at 7 to 8 years will fare less well on measures 1–4 than VLBW adults without early impairment [39].9.Young adults who had retinopathy of prematurity (ROP) and visual impairments at 7 to 8 years will have more adverse visual problems than those who had no ROP.10. Young adults who had neonatal chronic lung disease (CLD) will have more adverse respiratory function than those who no CLD11. Increased duration of breastfeeding will be associated with a small but measurable advantage in cognitive outcomes12. There will be increasing social and economic disadvantage with decreasing birthweight and increasing prematurity.

In our preliminary (Phase 1) study we re-established the cohort and began to address hypotheses 1–3. This Phase 2 study will extend the research to focus on health issues and neurocognitive outcomes but also to update the information collected as part of Phase 1.

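### The assurance that subdividing the VLBW group will not cost power is unsupported by the cohort's own subgroup sizes, and does not follow for testing differential effects

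*Protocol article*

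**What the plan says.** The power statement, in the section on statistical analysis and statistical power, rests on one comparison: "Assuming a minimum of 250 recruits from the VLBW cohort and 100 controls". With power set at 80% and a 5% significance level, this design is said to be able "to detect differences between groups of 30 SD or greater on continuous outcomes". The printed 30 SD is read here as 0.30 SD, assuming a lost decimal point.

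The same paragraph plans a further step, in which gestation is the last of three splitting factors (the quotation stops just before it): "The VLBW group may be further subdivided to test for differential effects by severity of disability at age 7 to 8, or by birthweight or". Later the paragraph reassures the reader that doing so, with prior disability as its example, "is unlikely to compromise study power since the effect sizes are likely to increase for more extreme groups". No figure accompanies that assurance.

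The figures needed to check it are under Study population, which compares survivors seen in Phase 1 with those not assessed. Among the 230 seen, 25.2% weighed under 1000 g and 24.8% were born before 28 weeks. For disability, the text reads "had moderate/severe disability at 7 to 8 years is 10.3 and 6.7", where the first number refers to those seen.

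**The concern.** The sentence treats a larger effect in an extreme group as sufficient to protect power. Three things are missing.

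- **Size of the offset.** The effect must grow enough to balance a much smaller group. The article does not say how much growth is needed or expected.
- **The right contrast.** The stated purpose is to look for differential effects. Two VLBW subgroups compared with the same controls differ in effect exactly when they differ from each other, because the control mean cancels. The relevant test is therefore between VLBW subgroups, and the 250 v 100 calculation says nothing about it.
- **The other subgroup.** For a given whole-group effect, a larger effect in one part means a smaller one in the rest.

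At stake is interpretation. Someone who relies on the sentence could take a non-significant subgroup contrast as evidence that disability, birthweight or gestation makes no difference, when the design had little chance of showing one.

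**Working it through.** **Inputs.** 250 VLBW, 100 controls, 80% power and alpha 0.05 come from the statistical section. Shares of 10.3%, 24.8% and 25.2% come from Study population. Assumptions: two-sided tests (sidedness is not stated), and Phase 1 shares that carry over to 250 recruits.

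**Subgroup sizes.** 0.103 × 250 ≈ 26; 0.248 × 250 = 62; 0.252 × 250 = 63. The remainders are 224, 188 and 187.

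**The plan's own figure first.** The detectable difference is d = (1.960 + 0.842) × √(1/n₁ + 1/n₂). For 250 v 100, d = 2.80 × 0.1183 = 0.331 SD (noncentral t: 0.332). The stated 0.30 SD is not reproduced two-sided, where its power is about 72%. One-sided, d is 0.294 SD. The stated odds-ratio range fits the two-sided reading better: I obtain 3.43 at a 5% base rate and 2.0 at 30%. I use two-sided figures from here.

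**Detectable differences (80% power, two-sided, noncentral t).**

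| Contrast | n₁ v n₂ | √(1/n₁ + 1/n₂) | d (SD) | Ratio to 0.332 |
|---|---|---|---|---|
| All VLBW v controls | 250 v 100 | 0.118 | 0.332 | 1.00 |
| Moderate/severe disability v controls | 26 v 100 | 0.220 | 0.622 | 1.87 |
| <28 weeks v controls | 62 v 100 | 0.162 | 0.456 | 1.37 |
| <1000 g v controls | 63 v 100 | 0.161 | 0.453 | 1.36 |
| Disability v rest of VLBW | 26 v 224 | 0.207 | 0.583 | – |
| <28 weeks v rest of VLBW | 62 v 188 | 0.147 | 0.412 | – |

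One-sided, the subgroup figures against controls are 0.40 to 0.55 SD, compared with 0.29 SD for the whole group. For dichotomous outcomes at a 30% base rate, the detectable odds ratio rises from 2.0 (n = 250) to 2.53 (n = 62) and 3.46 (n = 26).

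**Does growth in the extreme group rescue the differential test?** Grant the protocol's premise. Let the whole-group effect be 0.332 SD, and let the extreme-group effect grow just enough to keep 80% power against controls. The whole-group effect is the weighted mean of its parts, so:

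- <28 weeks: the rest average (250 × 0.332 − 62 × 0.456)/188 = 0.29 SD. Their power against controls is about 65%. The difference between the parts is 0.456 − 0.292 = 0.16 SD, and 62 v 188 has about 20% power to detect it.
- Disability: the rest average (250 × 0.332 − 26 × 0.622)/224 = 0.30 SD. Their power against controls is about 70%. The difference is 0.622 − 0.299 = 0.32 SD, and 26 v 224 has about 34% power.

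**Growth needed for 80% power on the differential test.** With the same whole-group effect, the extreme-group effect would have to be 0.332 + (188/250) × 0.412 = 0.64 SD for <28 weeks, or 0.332 + (224/250) × 0.583 = 0.85 SD for disability. These are 1.9 and 2.6 times the whole-group value. The required gaps of 0.41 and 0.58 SD stay the same whatever the whole-group effect is.

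**The case against.** The strongest reply is that the sentence makes a conditional argument. It does not say that the detectable difference stays constant; it says that larger effects will compensate. That can be true against controls. Power is 87% for 62 v 100 if the effect is 0.5 SD, and 95% for 26 v 100 if it is 0.8 SD. The Background reports that behavioural and school differences at 7 to 8 years grew as birthweight fell, and the statistical section expects effects above the detectable minimum. Holding the subgroup effect at 0.33 SD gives power of about 32% (n = 26) and 53% (n = 62), but that assumes the premise away. All of this stands. A reader might infer from the table that the protocol's statement is false. The documents do not support that, because they give no subgroup effect sizes. They report the childhood gradient without magnitudes, so they do not establish the offset either.

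A second reply also stands: the less extreme remainder loses almost nothing through numbers (188 v 100 gives 0.35 SD and 224 v 100 gives 0.34 SD). What it may lose is effect size, and that matters only if the whole-group effect is near the detectable minimum.

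Neither reply reaches the differential test. A large effect against controls is compatible with a small difference between VLBW subgroups.

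**Conclusion.** The assurance is unsupported for extreme groups against controls, and does not follow for differences between VLBW subgroups. Against controls, the subgroup effect must be about 1.4 times (gestation, birthweight) or 1.9 times (disability) the whole-group detectable effect to keep 80% power. Between subgroups, gaps of about 0.41 and 0.58 SD are needed. These sizes rest on Phase 1 shares carrying over, 250 recruits and two-sided tests. With 230 in place of 250, the figures against controls become slightly worse, at about 0.47 and 0.64 SD.

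Three wider readings should be resisted.

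- A reader might infer that the whole second aim depends on this sentence. It does not: the sentence belongs to the between-group analyses, and the separate trajectory paragraph allows regression and makes no power claim.
- A reader might extend the point to the MRI subsample or to the breastfeeding hypothesis, "Increased duration of breastfeeding will be associated with a small but measurable advantage in cognitive outcomes". The article claims no power for either, and it puts no number on that hypothesised advantage.
- A reader might conclude that hypotheses 8 to 10 should be recast with continuous predictors. They concern childhood disability or impairment, retinopathy and chronic lung disease. Birthweight or gestation would not test them, and replacing disability with IQ would change hypothesis 8.

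**What to change.** Replace the sentence with the detectable differences for each named split, stating the assumed subgroup sizes, two-sided 5% level and 80% power. Against 100 controls: about 0.62 SD for moderate/severe disability and 0.45–0.46 SD for <1000 g and <28 weeks. Within VLBW: about 0.58 SD (26 v 224) and 0.41 SD (62 v 188). Say that larger effects may preserve power against controls but not for differences between subgroups.

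For hypothesis 12, test the gradients with birthweight and gestation as continuous predictors, and keep subgroup tables as descriptive support. Add that a non-significant subgroup contrast will be reported with its confidence interval and not read as no effect.

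The cost is a few lines of text and a regression of a kind the plan already allows. No new data or participants are needed.
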